## Abstract

**Introduction:**

Physical inactivity is a major risk factor for a population's health, especially among socially disadvantaged groups. Many health promotion projects focus on increasing physical activity among their respective target groups. However, because they are mostly developed and implemented under laboratory conditions, they fail when being scaled to real-world settings. The community-based participatory research projects BIG and GESTALT have demonstrated their effectiveness regarding the physical activity promotion in real-world settings by employing a participatory method.

**Material and Analysis:**

Within the context of the BIG-5 and GET-10 projects, these previously implemented and tested participatory projects are scaled to 15 additional settings in Bavaria, Germany. By applying an overarching mixed-methods evaluation framework, the aim is to gain insights into a) the recruitment of communities for scale-up; b) the specific results of the projects according to the RE-AIM framework. In the recruitment of communities, standardized information on the first contact, the consultation process, the person in charge, and previously implemented health promotion projects are collected. A systematic web search will complete information on each community and their health promotion activities. Results will be compared with information on those communities most in need, here according to the deprivation index of communities in Bavaria, Germany. The scale-up process and its results will be measured using semi-structured interviews with project coordinators. A standardized questionnaire will be used with the course's participants. Applying the RE-AIM framework, the collected data will be analyzed deductively.

**Discussion:**

We expect the results to be highly relevant for the effective scale-up of any health promotion project. The study will enhance the understanding of how to reach those communities most in need of health promotion projects and will identify the barriers coordinators face in reaching socially disadvantaged groups.

**Conclusion:**

Although participatory projects are often used as individual projects, little is known about the scaling up of participatory health promotion projects. This cross-cutting evaluation of two projects aims at producing data on the barriers and facilitators for the reach of settings most in need, and those success factors for a durable implementation.

## Introduction

As in many other Western nations, physical inactivity is a major public health issue in Germany (1, 2). Physical inactivity influences population's health in many negative ways, such as being a cause of various non-communicable diseases, including type 2 diabetes, colon cancer, and breast cancer (3, 4). Recent studies have shown that population's physical activity (PA) levels have remained rather unchanged over time (5). In particular socially disadvantaged groups are less likely to meet the recommended level of PA set by the World Health Organization (6, 7).

To target these existing health inequalities, and in particular promote PA, the German Federal Ministry of Health has launched a policy initiative (“IN FORM”) in 2008 (8). This has resulted in numerous projects focusing on PA promotion for different target groups by using a diverse set of individual, setting-based, and also national-level health promotion endeavors (9). While many of these projects have been successful, they have also led to immediate discussion on how to scale “successful” pilot interventions in Germany to increase their public health impact (10, 11). These discussions match the international discourse on that topic (12–14). Scale-up is defined by the World Health Organization (15) as “deliberate efforts to increase the impact of successfully tested health innovations to benefit more people and to foster policy and program development on a lasting basis.” Factors that can lead to the successful scale-up of interventions have been identified by Yamey (16): (1) a simple and technically sound intervention, (2) strong leadership, (3) active engagement of various stakeholders and the target group, and (4) incorporated research. However, it has also been shown that, while scaling-up an intervention, observed effects might diminish, most likely due to adaptation processes (12).

These findings make research on how to scale proven PA interventions, and at the same time maintain their efficacy a relevant research topic. Thus far, only few studies have explored such questions in Germany, particularly for projects rooted in community-based participatory health promotion with the goal of promoting PA.

The two projects titled “*Bewegung als Investition in Gesundheit*” (BIG—interpreted as “Movement as investment in health”) and “*GEhen, Spielen und Tanzen Als Lebenlange Tätigkeit*” (GESTALT—interpreted as “Walking, playing, and dancing as lifelong activities”), described in this study protocol, lend themselves excellently to increase our understanding on the scale-up of such interventions. Both projects have demonstrated to be effective on the individual, policy, and environmental levels, and have succeeded in increasing PA levels among the socially disadvantaged groups of women in difficult life situations and older people with a risk for dementia (17, 18). The GESTALT project increased PA levels outside the class setting for 60% of its participants (17). The BIG project led to increased PA among women, while also having a positive impact on their blood pressure and stress levels (19). The project was able to implement a variety of PA classes according to the needs of the women living in the respective setting (20), hence contributing to their empowerment (21). Additionally, both projects have been, over the years, transferred to other communites. However, this scale-up has to date been rather slow, with an average of one additionally community per year adopting either BIG or GESTALT. Key lessons learned from the previous attempts to scale-up the BIG project have been described (18): This includes, the challenge of creating and maintaining structural support for the project work within community administrations, and having a “champion” for the project in the community. Strong facilitators for success are the continuous involvement of the target group in planning all project activities. For GESTALT, similar observations have been made.

The current study's protocol describes the efforts of the BIG-5 and GET-10 projects to scale up the previously implemented projects BIG and GESTALT to 15 new communities, and thus provide an opportunity to study in depth the facilitators and barriers of scaling-up community-based participatory research projects.

## Aims and Objectives

We aim at scaling up the two community-based participatory research interventions to an additional five (BIG-5) and 10 (GET-10) communities. To the best of our knowledge, this is the first study that includes two separate projects in their evaluation. In doing so, we aim at gaining knowledge on the following key questions, which can be organized into two areas.

### Recruiting Communities for Scale-Up

How do the communities and rural districts receive information on the two projects?Which communities intend to participate in the projects?Which barriers do communities face when applying for state-level funding for implementation?

### Results of Project Implementation

What are the health promotion capacities developed by communities during the project's implementation?What are the barriers and facilitators of communities for implementing the projects and for local capacity building?Do communities succeed in reaching the target population? If so, to what extent?

By including two projects, namely GET-10 and BIG-5, with a focus on different audiences, we will be able to compare the data regarding the efforts of communities to implement and maintain projects for the respective target groups. Additionally, it increases the chances to produce generalizable knowledge on scale-up and transfer of health promotion interventions.

## Projects and Funding

### BIG-5

The previous project BIG, which forms the foundation for BIG-5, was initiated in 2005. Its aim was to develop and implement exercise health promotion programs among women in difficult life situations. These women include low-income earners, ethnic minority members, the unemployed, those unable to work, and single mothers. BIG has been implemented in 17 communities, and its effects, efficiency, and long-term implementation have been evaluated regularly among the different settings (22). The project created low-barrier PA programs by adopting a participatory research method. By using this method, BIG intended to empower women to make decisions that positively influence their health. Currently, 7 out of the 17 communities were able to offer PA programs (18), with project activities being stopped on average after 4.2 years in 10 communities (18). In the context of BIG-5, our aim is to transfer the project to five additional communities (e.g., municipalities and rural districts) with a special focus on its permanent implementation.

To implement BIG-5, communities receive funding covering a part-time (20 h/week) coordinator position within the communities' administration, and yearly compensation for the voluntary efforts of three peers, to implement the participatory approach, PA classes, and constant advertisement for a period of up to 3.5 years. During funding a total of 18 different PA classes are meant to be implemented in each community. Peers mainly act as social catalysts to help reach out to and involve the target group. Coordinators will be in contact with and receive help from the scientific project team. Table 1 presents a detailed timeline of the BIG-5 project.

**Table 1 T1:** BIG-5 timeline of the project implementation by coordinators.

	**1st year**												**2nd year**												**3rd year**												**4th year**					

**Work-packages (WP)**	**I**			**II**			**III**			**IV**			**I**			**II**			**III**			**IV**			**I**			**II**			**III**			**IV**			**I**			**II**		
	1	2	3	4	5	6	7	8	9	10	11	12	13	14	15	16	17	18	19	20	21	22	23	24	25	26	27	28	29	30	31	32	33	34	35	36	37	38	39	40	41	42
**WP 1: Networking**																																										
Get in contact with potential partners																																										
Kick-off event																																										
Find participating peers																																										
Peer education																																										
**WP2: Analysis**																																										
Analysis of existing community data																																										
Development and execution of a target group need with peers																																										
**WP3: Planning**																																										
Cooperative planning																																										
Maintenance planning of BIG-5																																										
**WP 4: Implementation**																																										
Implementation of PA offers																																										
Training of new intercultural sport trainers																																										
Advertisement of offers																																										
**WP5: Evaluation**																																										
Self-evaluation of capacity building																																										
Participation semi-structured interviews																																										

*The grey shades are indicating the timeline for the several tasks*.

### GET-10

The first GESTALT project was developed and implemented in 2010 and acts as the foundation of GET-10. The project aimed at the prevention of dementia by enabling sedentary older people (above 65 years of age) to develop an active lifestyle. GESTALT has been previously implemented in 5 communities. The project implements an evidence-based 12-session exercise program (Appendix 1) (17). Additionally, trips to other existing exercise programs in the community and integrated health-related counseling are included in the GESTALT project. GET-10 is now transferring the GESTALT project to additional 10 communities that are implementing a total of 4 cycles per community of the pre-developed exercise program over the course of project funding. In addition to the pre-developed exercise programm, GET-10 will use the cooperative planning method (23, 24) to plan the sustainable implementation of the project within the communities from the very beginning. Compared with the BIG-5 project, GET-10 starts with a predeveloped exercise course (a detailed description is provided in Appendix 1). Instructors for the GESTALT program received a specific training course. Table 2 presents a detailed timeline of the GET-10 project.

**Table 2 T2:** GET-10 timeline of project implementation by coordinators.

	**1st year**												**2nd year**												**3rd year**												**4th year**					

**Work-packages (WP)**	**I**			**II**			**III**			**IV**			**I**			**II**			**III**			**IV**			**I**			**II**			**III**			**IV**			**I**			**II**		
	1	2	3	4	5	6	7	8	9	10	11	12	13	14	15	16	17	18	19	20	21	22	23	24	25	26	27	28	29	30	31	32	33	34	35	36	37	38	39	40	41	42
**WP 1: Networking and structures**																																										
Build a network																																										
Education of coordinators (8 workshops)																																										
Peer education																																										
**WP2: Analysis**																																										
Analysis of capacities of PA Promotion																																										
Adjustments for target group																																										
**WP3: Planning**																																										
Cooperative planning																																										
Maintenance planning of GET-10																																										
**WP 4: Implementation**																																										
GET-10 offer																																										
New offers																																										
Training of new trainers																																										
Advertisement of offers																																										
**WP5: Evaluation**																																										
Self-evaluation of capacity building																																										
Participation semi-structured interviews																																										

*The grey shades are indicating the timeline for the several tasks*.

## Methods and Analysis

The projects receive funding from the Federal Centre for Health Education. Communities located in Bavaria, Germany, with over 5,000 inhabitants can apply for funding for one of the projects by contacting the scientific coordinators. Using a low-threshold application scheme, communities have to send an expression of interest signed by the local major to the funding agency. Based on the expression of interest and some other formal criteria, communities receive funding.

During the project work, the 15 communities function as so-called “real-world laboratories” that “contribute to capacity development, new scientific insights and societal learning, building on iterations of experimentation and reflection” (25). In this process, real-world laboratories aim at meeting four characteristics: (1) follow transformative science approaches (e.g., testing out solutions to reduce health inequalities), (2) establish the mechanisms of coproduction between science and health promotion practice, (3) follow transdisciplinary approaches (i.e., scientific, policy, and practice) and to enable the target population to work together in finding possibilities of intervention implementation and sustainability of the project, and (4) plan for a durable scaling-up of implementation (26).

Communities will implement a predeveloped project plan for one of the two projects, as visualized in Tables 1, 2. During implementation, they will receive guidance and scientific support. Both projects are similar as both target disadvantaged population groups and adopt a participatory approach that enables communities to establish and sustain target group-specific interventions for PA. Using the participatory method of cooperative planning (23, 24), the projects aim to include members of the target group, researchers, community administrative staff, and practitioners (e.g., staff from local sport clubs or other health departments) in the planning and implementation of interventions for promoting PA among the target group. Coordinators will receive a manual on how to conduct the cooperative planning method (27), including a detailed description of all the steps. Based on the participatory nature of the projects, some actions taken may vary between the communities.

Coordinators also receive guidance and attend biannual workshops to share experiences among themselves. The workshops will be organized by the scientific team and cover topics such as (a) the cooperative planning method and coproduction of knowledge, (b) networking and capacity building, and (c) empowerment of the target group. Additional topics will be raised by coordinators. Because both projects follow the same participatory methodology, they work closely together and are connected during workshops and knowledge-exchange meetings.

Both projects have been approved by the ethics committee of FAU, Germany (520_20Bc). All participants who are involved will be informed about the voluntary nature of participation in any scientific data collection and their right to withdraw their consent at any time without having to provide a reason.

To answer the research questions in the three areas mentioned above, a convergent parallel mixed methods approach (28) will be applied. We will use concurrent implementation of quantitative and qualitative strands which will be compared and related during the analysis to consolidate our findings.

### Recruiting Communities for Scale-Up

To evaluate the recruitment process of the communities, all contact between the researchers and the interested community members will be systematically documented. Interested community members will engage in one-on-one phone calls with researchers. During the call, the researchers will ask standardized questions to gather information on (a) how the communities learned about the projects (e.g., via newsletters, social media posts, or through colleagues), (b) who contacted the researchers (e.g., mayor, health department, external partner, etc.), (c) why they were interested in the project, and d) if they had previous experience or carried out similar projects in the past.

Additionally, data will be collected on all the interactions with the communities until they have made a final decision to take part. This will include (a) the time it took, (b) the number of contacts, and (c) the factors that the communities mentioned as influencing their decision.

A systematic web and database search and qualitative content analysis, here according to McMillan et al. (29), will complement the systematic documentation by identifying each community's (1) population size, (2) community deprivation index developed by Kroll (30), (3) previously implemented health promotion programs, and (4) the percentage of target population among inhabitants and other potentially relevant factors (e.g., party alignment in city councils). To generate additional data on the communities most in need, the community deprivation index will be utilized (30).

The collected data will be analyzed using qualitative content analysis (31) to make comparisons among the following three groups: (a) participating communities, (b) interested communities that did not apply for funding, and (c) communities most in need according to the community deprivation index that match the funding criteria (located in Bavaria with inhabitants totaling over 5,000).

The analysis will identify the time period needed by communities to reach a decision, barriers and facilitators that led to the decision, number of already existing health-promotion projects in the communities, and whether socioeconomically deprived communities are being reached by the funding scheme.

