### Results of Project's Implementation

To answer the research questions regarding the effectiveness of the projects, we utilize the RE-AIM framework and its five dimensions: “reach,” “efficacy,” “adoption,” “implementation,” and “maintenance” (32). Using the RE-AIM framework allows us to address our research questions in regard to the ability of communities to generate public health impact by implementing the two exercise interventions which are targeted at vulnerable groups. Additionally, as mentioned by Kwan et al. (33) it “provides structure to systematically evaluate health program impact.”

We will conduct annual semi-structured interviews with the project's coordinators of the 15 communities (*n* = 45 interviews), as well as annual semi-structured focus groups with peers (*n* = 30 interviews) in each setting. Additionally, quantitative data will be collected, including an annual evaluation of capacity building using a standardized questionnaire filled out by the projects' coordinators, all attendance lists of the BIG-5 and GET-10 exercise courses, including number of people on the waiting lists, and data on satisfaction using a standardized short feedback questionnaire filled out by the course participants. Table 3 describes all study evaluation methods, participants, and study parameters.

**Table 3 T3:** Evaluation methods.

		**Participants**	**Time of measurement**	**Topics of interest**	**Total**	**RE-AIM indicator**
Recruiting communities for scale-up	Semi-structured telephone interviews	All interested communities		- Who contacted the researcher? - How did they receive information? - Is there a specific reason why they want to implement the project? - Do they have previous or similar health promotion projects?		-
	Timeline documentation	All interested communities	From first contact until decision making or project implementation	- How long do communities take until making a decision? - Do we reach communities that are the most in need?		-
	Web-based search	Participating communities + interested communities + 10 most deprived Bavarian communities		- How active are communities regarding health promotion? - Do we reach communities that are the most in need? - Percentage of the target population in the community		-

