## Conclusion

Scale-up and sustainment of community-based participatory research projects is crucial to reduce health inequalities. The two interventions have already been evaluated and demonstrated effectiveness. The current study can provide additional evidence on the barriers and facilitators of scale-up and sustainability, capacity building within a community setting through health promotion projects, and the project's effects on the target populations. Through a cross-sectional examination of the recruitment process of communities, the current study will be the first to provide evidence on how to reach communities to engage in such projects and the barriers and facilitators for implementation they may face.

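### Information channels are recorded only for communities that made contact, so the data describe how enquirers heard of the projects but not how well any channel reaches communities

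*Protocol article*

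**What the plan says.** The first recruitment question under Aims and Objectives is put about communities in general: "How do the communities and rural districts receive information on the two projects". Methods and Analysis makes entry depend on the community's own approach: Bavarian communities "with over 5,000 inhabitants can apply for funding for one of the projects by contacting the scientific coordinators".

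The recruitment part of Methods and Analysis then says what is recorded. It states that "all contact between the researchers and the interested community members will be systematically documented", and: "Interested community members will engage in one-on-one phone calls with researchers." In those calls researchers ask, among other things, "how the communities learned about the projects (e.g., via newsletters, social media posts, or through colleagues".

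Table 3 agrees. The telephone interviews cover all interested communities and include the item on how they received information. The timeline documentation runs "From first contact until decision making or project implementation". The web search covers "Participating communities + interested communities + 10 most deprived Bavarian communities"; its topics are health-promotion activity, whether the communities most in need are reached, and the target population's share. The text introduces Table 3 as covering every evaluation method of the study.

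On what will follow from these data, the Conclusion says that "the current study will be the first to provide evidence on how to reach communities to engage in such projects". The Discussion part of the abstract expects a better understanding of how to reach the communities most in need, and the abstract's Conclusion speaks of barriers and facilitators for reaching such settings.

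**The concern.** Every answer about channels comes from a community for which the information did lead to contact. The answers are thus selected on the outcome that the study wants to understand. Nothing in the listed methods shows which communities were addressed, by which channel, and stayed silent.

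Two things are at stake. First, advice for later scale-up on how to reach communities needs some view of those who were addressed and did not respond, and the plan collects none. Second, the plan wants to know whether the funding scheme reaches deprived communities. If such a community does not appear among the enquirers, the cause may be that it never heard of the projects or that it heard and did not act. The first points to dissemination, the second to barriers to applying, and the data as described cannot separate them.

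**Working it through.** The document gives no channel figure to reproduce, so the check is first a comparison of the recruitment data sources and then a short illustration.

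**Step 1: what each source covers (Table 3 and the recruitment text in Methods and Analysis).**

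| Source | Communities covered | Whether or how they were informed | Outreach sent by the team |
|---|---|---|---|
| Telephone interviews | All interested | Yes, by self-report | Not listed |
| Timeline documentation | All interested, from first contact | No | Not listed |
| Web search | Participating, interested, 10 most deprived | No | Not listed |

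Only the web search includes communities that never made contact, and it has no item on whether they were informed. Newsletters, social media posts and colleagues appear only as example answers in the phone call. The text does not say what was sent, when, or to whom.

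**Step 2: what can be estimated for a channel.** The contact rate of a channel is

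rate = contacts through the channel / communities addressed through the channel.

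The numerator can be taken from the phone calls. The denominator comes from no listed source. To show what this means, assume 12 contacts through channel A and 6 through channel B. All figures in this table are assumptions, none comes from the document.

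| Addressed, A | Addressed, B | Rate A | Rate B | Ratio A/B |
|---|---|---|---|---|
| 60 | 60 | 12/60 = 0.20 | 6/60 = 0.10 | 2.0 |
| 100 | 50 | 12/100 = 0.12 | 6/50 = 0.12 | 1.0 |
| 200 | 30 | 12/200 = 0.06 | 6/30 = 0.20 | 0.30 |
| 300 | 15 | 12/300 = 0.04 | 6/15 = 0.40 | 0.10 |
| 30 | 200 | 12/30 = 0.40 | 6/200 = 0.03 | 13.3 |

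The same contacts fit either order of the two channels. The range of 0.10 to 13.3 reflects the chosen denominators. It is not an estimate of any error in this study.

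**Step 3: the most deprived communities.** Table 3 takes 10 of them. Assume that none enquires, and let k be the number that had been informed. Then k can be anything from 0 to 10:

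- k = 0: nobody was informed, and no response rate exists (0/0).
- k = 10: all were informed, and the response is 0/10 = 0%.

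The study's record is the same for all values of k: no contact, no channel answer, and a web-search entry without an item on exposure. If some of the 10 do enquire, the argument holds for the rest.

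**The case against.** The strongest reply is that the plan never sets out to compare channels. It announces qualitative content analysis, and the results it lists are time to decision, barriers and facilitators behind the decision, existing health-promotion projects, and whether deprived communities are reached. A reader might infer that channels will be counted and ranked, and that the advice could end up favouring the weakest one. The documents do not support that reading: no counts, rankings or contact rates are announced. The question under Aims and Objectives is descriptive, and for enquiring communities it is answered. This part of the objection stands. It does not remove the point, because content analysis of the same answers lacks the same comparator.

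Second, evidence on reaching communities also comes from who made contact, why, how long the decision took, and the comparison with interested communities that did not apply. The Conclusion's sentence refers to the recruitment process as a whole and does not mention channels. That is fair, but those sources also begin with communities that showed interest. Only the web search goes further, and it has no item on exposure.

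Third, an article condenses a fuller protocol, and mailing lists are operational records. A reader might infer that the team keeps no record of its outreach. The article does not show that, and such records may well exist. What can be said is narrower: Table 3 is presented as complete, no such record is among the evaluation data, and the claims about reach stand in this same document.

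Fourth, the remedy is partial. Of the three example channels, only newsletters would clearly have a recipient list. This stands and limits what the fix can deliver.

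**Conclusion.** The point holds in a limited form. As described, the data can show how enquiring communities heard of the projects. They cannot show how well any channel reaches communities, and they cannot tell a deprived community that was never informed from one that was informed and did not respond. The claims about reach in the abstract's Discussion and Conclusion and in the main Conclusion go further than this.

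The size of any distortion is unknown. The document gives neither the number of eligible communities nor the number addressed, and the ratios shown above rest wholly on assumed figures. No stated number, planned test or sample size is affected.

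The verdict assumes that Table 3 is complete, as the text says, and that no outreach record kept elsewhere is meant to enter the evaluation. If such a record exists and will be used, the point reduces to saying so in the plan. It is a cheap improvement, not a flaw that undermines the study.

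**What to change.** Extend the recruitment documentation in Methods and Analysis to the team's own directed outreach: date, channel and communities addressed. Where recruitment has already begun, rebuild this from mailing lists and send records. Match the log to the eligible communities (Bavaria, over 5,000 inhabitants) and to their deprivation index.

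Then report, for the participating, the interested but not applying, and the most deprived communities, whether each had been addressed. Give contacts per communities addressed only for channels that have a recipient list. For social media and word of mouth, report description only and state that no rate can be given.

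If no log can be rebuilt, limit the claims in the abstract's Discussion and Conclusion and in the main Conclusion to how enquiring communities heard of the projects.

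The cost is a small documentation effort by the team. Several channels will still have no denominator, so the log will separate uninformed from unresponsive communities only as far as directed outreach is concerned.
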